## Abstract

**Background:**

Venous thromboembolism (VTE) is a common complication of critical illness with important clinical consequences. The Prophylaxis for ThromboEmbolism in Critical Care Trial (PROTECT) is a multicenter, blinded, randomized controlled trial comparing the effectiveness of the two most common pharmocoprevention strategies, unfractionated heparin (UFH) and low molecular weight heparin (LMWH) dalteparin, in medical-surgical patients in the intensive care unit (ICU). E-PROTECT is a prospective and concurrent economic evaluation of the PROTECT trial.

**Methods/Design:**

The primary objective of E-PROTECT is to identify and quantify the total (direct and indirect, variable and fixed) costs associated with the management of critically ill patients participating in the PROTECT trial, and, to combine costs and outcome results to determine the incremental cost-effectiveness of LMWH versus UFH, from the acute healthcare system perspective, over a data-rich time horizon of ICU admission and hospital admission. We derive baseline characteristics and probabilities of in-ICU and in-hospital events from all enrolled patients. Total costs are derived from centers, proportional to the numbers of patients enrolled in each country. Direct costs include medication, physician and other personnel costs, diagnostic radiology and laboratory testing, operative and non-operative procedures, costs associated with bleeding, transfusions and treatment-related complications. Indirect costs include ICU and hospital ward overhead costs. Outcomes are the ratio of incremental costs per incremental effects of LMWH versus UFH during hospitalization; incremental cost to prevent a thrombosis at any site (primary outcome); incremental cost to prevent a pulmonary embolism, deep vein thrombosis, major bleeding event or episode of heparin-induced thrombocytopenia (secondary outcomes) and incremental cost per life-year gained (tertiary outcome). Pre-specified subgroups and sensitivity analyses will be performed and confidence intervals for the estimates of incremental cost-effectiveness will be obtained using bootstrapping.

**Discussion:**

This economic evaluation employs a prospective costing methodology concurrent with a randomized controlled blinded clinical trial, with a pre-specified analytic plan, outcome measures, subgroup and sensitivity analyses. This economic evaluation has received only peer-reviewed funding and funders will not play a role in the generation, analysis or decision to submit the manuscripts for publication.

**Trial registration:**

Clinicaltrials.gov Identifier: NCT00182143. Date of registration: 10 September 2005.

**Electronic supplementary material:**

The online version of this article (doi:10.1186/1745-6215-15-502) contains supplementary material, which is available to authorized users.

## Background

Venous thromboembolism (VTE) is a common complication of critical illness and has important clinical consequences, including deep vein thrombosis (DVT), pulmonary embolism (PE), increased length of stay in the intensive care unit (ICU) and hospital and death [1–3]. Although DVT has potentially serious consequences, it is often unrecognized in the ICU as the clinical examination for DVT lacks sensitivity and specificity [4]. Further, routine ultrasound screening for DVT is not a cost-effective diagnostic strategy in practice [5]. Thus, thromboprophylaxis is the most appropriate mechanism to prevent VTE and its complications among critically ill patients.

We have previously documented that most economic evaluations of VTE strategies are designed after the results of the trial are known, and are funded by the manufacturers of the agents compared [6]. This introduces the opportunity for biased design and interpretation of economic evaluations. Therefore, we designed the economic evaluation (E-PROTECT) of a multicenter randomized, blinded controlled trial of 3,746 patients comparing the effectiveness of unfractionated heparin (UFH) and low molecular weight heparin (LMWH) (dalteparin) [7]. The primary objective of E-PROTECT is to identify and quantify the total (direct and indirect, variable and fixed) costs associated with the management of critically ill patients participating in the PROTECT trial, and to combine costs and outcome results to determine the incremental cost-effectiveness of LMWH versus UFH, from the acute healthcare system perspective, over a data-rich time horizon of the ICU admission and hospital admission.

## Methods/Design

### E-PROTECT background studies and methodologies

#### The PROTECT trial

The objective of the Canadian Institutes of Health Research (CIHR)-funded PROTECT trial [7, 8] was to evaluate LMWH versus UFH on the primary outcome of the incidence of proximal leg DVT diagnosed by compression ultrasound, with secondary outcomes of PE, venous thrombosis at any site, bleeding and heparin-induced thrombocytopenia (HIT). The study design was a randomized, stratified, concealed double-blind multicenter trial with enrolment throughout Canada, Australia, the United States, Saudi Arabia, the United Kingdom and Brazil. The PROTECT trial enrolled 3,746 critically ill patients between May 2006 and June 2010 according to previously published eligibility criteria [7, 8]. A central computerized web-based or phone-in randomization system ensured concealed randomization of patients to either dalteparin 5,000 international units (IU) daily or UFH 5,000 IU twice daily subcutaneously for the ICU stay. Only the research pharmacist at each participating centre was aware of the allocation. Bilateral proximal leg compression ultrasounds were performed within 48 hours of ICU admission, twice weekly and on DVT suspicion. A predefined algorithm was used to diagnose PE; bleeding, HIT, other thrombosis and complications were identified using *a priori* definitions and procedures. The PROTECT publication itself provides complete study data [7].

#### The E-PROTECT pilot study

To first determine the feasibility of obtaining patient-specific line-item costing (for each aspect of care delivery), we conducted a pilot study between 2006 and 2007 involving six hospitals in Canada, the United States and Australia [9]. However, we discovered that in both privately funded and publically funded institutions, the variability around patient costing was substantial and that line-item costs were not routinely available. Many costs were ‘rolled up’ into summary cost measures, and subsequently, this methodology would not allow for a linkage of costs and clinical events to be measured as part of the PROTECT trial case report form. Therefore, we designed a more appropriate cost gathering methodology to capture hospital-specific line-item costs according to important variables that we anticipated will drive costs and possible cost-effectiveness (Additional file 1).

In order to determine such cost drivers, we performed a systematic review of economic analyses of thromboprophylaxis strategies in hospitalized patients to identify variables that we anticipate will drive costs and possible cost-effectiveness in E-PROTECT, and to determine potential ranges for willingness-to-pay to avoid DVT and PE [6]. From 5,180 potentially relevant studies, 39 met the eligibility criteria from which we extracted data on study characteristics, quality, costs and efficacy. In addition to identifying variables likely to be influential in E-PROTECT, we found that LMWHs appear to be the most economically attractive drugs for VTE prevention in acutely ill hospitalized patients, whereas newer agents may be more economically attractive in patients receiving joint replacement surgeries. However, the manufacturer of the new agent supported approximately two-thirds of evaluations and such drugs were likely to be reported as economically favorable. Incremental cost-effectiveness ratios to prevent VTE events ranged from a dominance of LMWH to under $5,000 per VTE event avoided [6].

### E-PROTECT methods

#### E-PROTECT design and economic assumptions

We designed E-PROTECT before the results of the PROTECT trial were known. Study funding was from peer-reviewed sources and none of the funders played a role in the generation, analysis or decision to submit the economic evaluation for publication. We developed our analysis according to established guidelines [10–14]. Also, we used an acute healthcare system perspective (during the period of hospitalization) to encompass all in-patient direct medical and hospital costs, including physician and other personnel costs. Our preliminary analytic plan was pre-specified with public study funders (Heart and Stroke Foundation, Ontario, Canada) as part of the economic evaluation of the PROTECT trial protocol prior to completion of the trial and unblinding of the economic consequences of clinical data.

#### E-PROTECT patients, outcomes and effects

No patients were lost to follow-up. Although the PROTECT trial considered both intention-to-treat and on-treatment analyses, primary outcomes were based on adherence to the intention-to-treat principle and will form the clinical event estimates of the economic analyses. We recorded the frequency of DVT, PE, major bleeding and HIT among all patients to measure the primary clinical incremental effect of the difference in any VTE (all limb DVT, PE and non-limb thromboses), and secondary clinical incremental effects of episodes of PE, DVT, major bleeding and HIT. The PROTECT trial was designed and powered to evaluate differences in the rate of thrombotic events between two pharmacologic thromboprophylaxis strategies, not differences in life expectancy; accordingly, incremental differences in life years are not primary outcomes in this economic evaluation. All measures of clinical events, medications administered, laboratory and radiology testing, complications, blood product transfusions, procedures and surgeries and duration of ventilation, ICU and hospital stay were recorded alongside the PROTECT trial as part of the study case report form [7, 8].

### E-PROTECT costs

#### Total, direct and indirect costs

Total costs for patients in the PROTECT trial comprise direct and indirect costs [15]. To determine which cost to include, we performed a systematic review of the VTE cost-effectiveness literature [6] for hospitalized patients, and reviewed evidence underlying the relative importance among the E-PROTECT Steering Committee, before deciding upon final cost variables. Direct costs are attributable to medications, transfusions, laboratory or radiology tests or procedures or personnel directly associated with specific components of patient care. Such costs can usually be determined on an item-by-item, procedure-by-procedure basis. Indirect costs are those for services or procedures that often benefit more than one patient at a time and their precise benefits to specific patients are often difficult to trace, such as maintenance of equipment and infrastructure. A large proportion of such indirect costs comprise the ‘overhead’ in operating an ICU, laboratory or pharmacy, for example [10, 15, 16]. These costs can be fixed (roughly the same amount on a recurring basis), or variable (fluctuating depending upon patient circumstances and course). E-PROTECT measured both direct and estimated indirect costs at study sites.

#### Direct costs from participating sites

Direct and indirect costs were sought from 23 of 67 hospitals and five of six countries participating in the PROTECT trial (12 hospitals in Canada; five hospitals in Australia; three hospitals in the United States; two hospitals in Saudi Arabia; one hospital in Brazil). Sites will be invited to participate in the costing component of the economic evaluation to reflect overall proportions of patients enrolled in the PROTECT trial among all participating countries. Direct costs will be divided among the following categories: 1) study-related drugs (unfractionated heparin, dalteparin, enoxaparin, tinzaparin, other low molecular weight heparins, protamine, Desmopressin (DDAVP), aprotinin, aminocaproic acid, danaparoid, lepirudin, argatroban, fondaparinux, activated Factor VII, acetyl salicylic acid (ASA), clopidogrel, a representative proton-pump inhibitor (pantoprazole), vitamin K, warfarin and epinephrine for injection or infusion); 2) laboratory testing (complete blood count, electrolytes, creatinine, blood urea nitrogen, arterial blood gas, partial thromboplastin and prothrombin time, anti-Xa level, enzyme-linked immunosorbent assay (ELISA) and serotonin release HIT assay); 3) personnel (including *per diem* most responsible physician and per consultation physician charges over the course of an ICU and hospital admission, nursing, pharmacist, respiratory therapist, physical therapist, social work and ICU administrative and/or clerical staffing hourly wage range); 4) radiology (unilateral and bilateral leg compression ultrasonography and venography, portable chest radiograph, computerized tomography (CT) scan of the chest with an angiogram (pulmonary embolism protocol), CT scan of the abdomen, pelvis, and head, pulmonary angiogram and ventilation-perfusion scan); 5) procedural costs (electrocardiogram, central venous catheter material costs, inferior vena cava filter material and insertion and removal costs, naso- or oro-gastric tube, procedure costs for gastroscopy, colonoscopy, bronchoscopy, and angiography with embolization and intermittent and continuous renal replacement therapy); and, 6) operative costs for laparotomy (including the surgeon and surgical assistant, anesthesiology and nursing personnel costs).

Operative and bedside surgical procedures were classified according to procedure and body site (head and neck, cardiac, vascular, thoracic, gastrointestinal, orthopedic, genitourinary, plastic, neurosurgical or other), by two independent adjudicators, blinded to treatment allocation, with separate attribution as to whether the procedure was conceivably precipitated or related to the study drug (bleeding or thromboses). Disagreements were resolved by consensus or a third reviewer. Rates of all surgeries and study drug-related surgeries will be compared for each study group and those we believe to be possibly related to the study drug will be included in the cost analysis.

#### Direct costs associated with heparin-induced thrombocytopenia

As episodes of HIT with thrombosis (HITT) and without thrombosis involve complex and expensive investigation and treatment, some authors previously performed a single-center micro-costing study in one PROTECT trial center. They aimed to estimate the total average attributable costs of an episode of HIT (and HITT including arterial and venous thromboses), as well as associated HIT-safe anticoagulants, associated bleeding and specialized HIT diagnostic testing. The details of the micro-costing study are published elsewhere [17] but included diagnosis, investigation, treatment and administration costs. However, for E-PROTECT, we will capture costs and measures of resource use for complications such as bleeding, HIT and HITT as part of the PROTECT case report and centre-specific E-PROTECT costs, and will not assign additional HIT or bleeding-specific costs in order to avoid double counting. Bleeding and blood product transfusion services costs (per unit of red blood cells, frozen plasma and thawing, cryoprecipitate, cross matching and platelets and associated laboratory testing of blood type and screen) were derived from a Canadian national transfusion resource, education and costing exercise [18].

#### Prophylactic and therapeutic anticoagulation outside the ICU

Ward-based prophylactic and therapeutic anticoagulation was not directly measured; therefore, we will make the following assumptions:If no therapeutic anticoagulation was used in last two days in ICU, we will assume UFH prophylaxis will be used for the entire ward stay;If warfarin was used in last two days in ICU, we will assume that warfarin will be used for entire ward stay;If treatment doses of LMWH were used in last two days in ICU, we will assume that treatment with LMWH will continue for five days on the ward, followed by warfarin for the remainder of the hospital stay;If treatment doses of UFH were used in last two days in ICU, we will assume that treatment with UFH occurs for five days on the ward, followed by warfarin for the remainder of the hospital stay;If treatment doses of danaparoid or other HIT-safe anticoagulants were used in last two days in ICU, we will assume that treatment with danaparoid or other HIT-safe anticoagulants occurs for five days on the ward, followed by warfarin for the remainder of the hospital stay.

#### Indirect costs - ICU and ward care

We will measure institution-specific estimates of indirect (overhead) costs per day of care in the center’s highest acuity ICU (capable of providing ventilation and hemodynamic support), and for patients receiving care on standard medical and surgical wards. From the E-PROTECT pilot, we found that each institution determined this cost per day in a unique fashion, but generally comprised components of non-physician personnel cost, equipment maintenance, some diagnostic testing and ICU and other ward overhead infrastructure costs [9]. This rolled-up indirect per day cost will be determined to estimate the difference between the total of individual direct costs relevant for patients in the PROTECT trial (above), and the total daily costs of care that may reflect additional and indirect costs which are important in determining total costs, but are difficult to capture as single variables.

Mean institutional costs of ICU care typically represent very high costs on the first day, and substantially lower (one-quarter) costs after the second day [16], with a further decrease after discharge to a ward bed. Using our hospital estimates of indirect costs in ICUs and on the ward, and in accordance with prior literature, we will apply a ratio of 1 (hospital ward):2.5 (ICU day two onwards):4 (ICU day one) [16, 19–21]. Most daily costs of care in ICUs are fixed, not variable, and prior work has demonstrated minimal direct-variable cost differences due to ventilation status [16]. Because of this and because the vast majority of ICU days represent days patients received mechanical ventilation, we will apply a small incremental (between 3 and 5%) daily indirect cost due to this advanced life support [16].

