### E-PROTECT sensitivity analyses

As patient characteristics, effects and costs may differ outside of tightly controlled clinical trials and in various jurisdictions, we plan a number of sensitivity analyses to explore how incremental cost-effectiveness ratios may change with plausible differences in values, including costs of LMWH and UFH, and per day cost of care in ICU and hospital wards. We will also perform sensitivity analyses using the efficacy analysis of the PROTECT trial that considered only patients who received the study drug for two days or more and had two or more leg compression ultrasounds, and by considering only symptomatic thromboses. Multi-way sensitivity analyses will be performed by varying the estimates of pairs of potentially influential variables. We will perform a probabilistic sensitivity analysis of pairs of known costs and effects from the PROTECT trial, using bootstrapping techniques, among 1,000 samples, with replacement, in order to generate an incremental cost-effectiveness plot [26, 27].

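### The ICU day-cost ratio to be applied (1:2.5:4) does not match the one-quarter figure offered in its support, and the plan does not say which measured overhead anchors it

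*Protocol article*

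**What the plan says.** All but one of the statements come from the protocol article, section 'Indirect costs - ICU and ward care'.

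- Each hospital supplies overhead figures: "We will measure institution-specific estimates of indirect (overhead) costs per day of care", for its highest-acuity ICU and for standard wards.
- Background on the shape of ICU cost, citing reference 16: "very high costs on the first day, and substantially lower (one-quarter) costs after the second day", "with a further decrease after discharge to a ward bed".
- The instruction: "we will apply a ratio of 1 (hospital ward):2.5 (ICU day two onwards):4 (ICU day one) [16, 19–21". It is introduced with the words "Using our hospital estimates of indirect costs in ICUs and on the ward, and in accordance with prior literature". Reference 16 is therefore cited both for the background figure and for the ratio.
- A remark on cost structure: "Most daily costs of care in ICUs are fixed, not variable".

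The section on sensitivity analyses lists the inputs to be varied, "including costs of LMWH and UFH, and per day cost of care in ICU and hospital wards". It does not name the step from ICU day one to later ICU days.

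**The concern.** Two adjacent sentences give a different size and a different starting day for the fall in ICU cost, yet the second is presented as agreeing with the literature behind the first. The ratio is a costing input: the analytic plan multiplies per-day costs by length of stay in the ICU and hospital. If the ratio is wrong, the price of every ICU day after the first is wrong, and total cost per patient with it. If the background figure is wrong, or describes another quantity, the ratio is left without a stated justification.

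A second gap adds to this. The hospitals supply a measured ICU overhead and a measured ward overhead per day. Those two figures already fix one ICU-to-ward relation, and the ratio fixes another. The article does not say whether the ratio hangs on the ward figure, on the ICU figure as a day-one cost, on the ICU figure as a later-day cost, or on the ICU figure as an average over the stay.

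**Working it through.** **Inputs.** Ward 1, ICU from day two 2.5, ICU day one 4; one-quarter, with onset after the second day. All are from the indirect-cost section. ICU stays of 9 and 14 days are my assumptions; the article gives no length of stay.

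**Step 1: does the ratio reproduce one-quarter?**

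- Later ICU day / day one = 2.5/4 = 0.625, a fall of 37.5%.
- A fall to one-quarter needs 4 × 0.25 = 1.0. That equals the ward value, so no further decrease on the ward would remain.
- A fall by one-quarter needs 4 × 0.75 = 3.0.
- Ward / day one = 1/4 = 0.25. This is the only pair in the ratio that gives one-quarter, but the text places that figure inside the ICU stay.

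Neither reading is reproduced. The onset differs too: the text's lower cost begins after day two, the ratio's on day two.

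**Step 2: whole-stay cost with day one held at 4 ward units.** For a stay of L days:

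- Ratio as written: 4 + 2.5(L − 1).
- To one-quarter, day two already at 1: 4 + (L − 1).
- To one-quarter, day two at 2.5: 4 + 2.5 + (L − 2).
- To one-quarter, day two at 4: 4 + 4 + (L − 2).
- By one-quarter from day two: 4 + 3(L − 1).

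| Version | L = 9 | L = 14 |
|---|---|---|
| Ratio as written | 24.0 | 36.5 |
| To one-quarter, day two at 1 | 12.0 | 17.0 |
| To one-quarter, day two at 2.5 | 13.5 | 18.5 |
| To one-quarter, day two at 4 | 15.0 | 20.0 |
| By one-quarter from day two | 28.0 | 43.0 |

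The ratio gives 1.6 to 2.0 times the to-one-quarter total at 9 days (24/15, 24/12) and 1.8 to 2.1 times at 14 days (36.5/20, 36.5/17).

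The choice of anchor matters. If the later day is held at 2.5 and day one becomes 10, the 9-day total is 10 + 8 × 2.5 = 30, which is 25% above 24, and the later-day price does not change.

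**Step 3: cost of a later ICU day when each version is scaled to the same measured average.** Later-day value divided by (whole-stay total / L):

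- L = 9, ratio: 2.5/(24/9) = 0.94. To one-quarter: 1/(12/9) = 0.75, 1/(13.5/9) = 0.67, 1/(15/9) = 0.60. Gap: 1.25, 1.41 and 1.56-fold.
- L = 14, ratio: 2.5/(36.5/14) = 0.96. To one-quarter: 0.82, 0.76, 0.70. Gap: 1.16, 1.27 and 1.37-fold.
- By one-quarter, L = 9: 3/(28/9) = 0.96 against 0.94, so almost no gap.

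**Step 4: effect of the unstated anchor, ratio unchanged.** Suppose the measured ICU figure is the average over a 9-day stay, so that the true total is 9 measured days.

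- Assigned to later days (2.5): 24/2.5 = 9.6 measured days, +7%.
- Assigned to day one (4): 24/4 = 6.0 measured days, −33%.
- Anchored on the ward figure: the ICU measurement is not used.

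**The case against.** The strongest reply is that the two sentences may describe different quantities. The background sentence speaks of institutional ICU cost in general; the ratio applies to indirect cost and draws on the hospitals' own estimates and three further references. This stands as a possibility, but the article does not say so and cites the same source for both. It is also hard to fit with the rest of the section. If indirect cost stays at 62.5% of its day-one level, total cost can fall to 25% only if indirect cost is at most 0.25/0.625 = 40% of day-one cost, with later direct cost at zero at that limit. That sits poorly with the remark that most ICU cost is fixed, although fixed and indirect are not the same thing.

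Some stronger inferences are tempting and are not supported:

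- **That the base case is undefined.** It is not: the ratio is an explicit instruction, and one-quarter is background.
- **That early ICU intensity is counted twice.** The section defines the rolled-up overhead as what remains between itemised direct costs and total daily cost, and the Discussion commits to avoiding double counting. A day profile laid on that residual does not double count if it is scaled to it.
- **That the arms differ mainly in ICU and ward days, making this the dominant input.** No length of stay by arm is given.
- **That a later ICU day is misjudged 2.5-fold (2.5 against 1.0).** This holds only with day one fixed at 4 ward units.
- **That the gradient should be dropped from the base case.** That would be a preference; nothing in the text requires it.

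The planned sensitivity analyses help in part. Varying ICU and ward day costs separately, in pairs and in a Tornado diagram changes the ICU-to-ward relation. It does not reach the step between day one and later days.

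**Conclusion.** The discrepancy is real under both readings of one-quarter, and the onset day differs as well. Nothing else in the article reconciles them. It is an unexplained mismatch between an operative input and its stated support; it does not prove the ratio wrong, because the cited sources and the costing manual (Additional file 1) are not at hand. The missing anchor is a separate gap that remains even if the ratio is right.

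For an assumed 9-day stay, whole-stay overhead is 24.0 units under the ratio against 12.0 to 15.0 under a fall to one-quarter, with day one held at 4 ward units. On a common measured average, the later-day price differs about 1.25 to 1.56-fold at 9 days and 1.16 to 1.37-fold at 14. Under a fall by one-quarter, the scaled gap is negligible. Because the same ratio applies in both arms, incremental cost moves only through differences between arms in length of stay; total cost per patient moves directly. The point is worth settling before the costing is closed.

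**What to change.** 1. Check reference 16 and make the text and the ratio agree on three things: the figure, the type of cost it describes (total or indirect), and the day on which the lower cost begins.
2. State the anchor. If the gradient is kept, scale it so that the average over the observed ICU stay equals the measured ICU overhead per day, and cost ward days at the measured ward overhead.
3. Add the alternative day-one to later-day gradient as a named sensitivity analysis alongside the planned variation of per-day costs.

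The cost is a few sentences and a recalculation from data already sought. The 'Trial status' section says the costing was not complete at submission and allows further analyses with justification.
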